**New in this study**

- Evaluation of the overnight closed loop algorithms based on MPC in children between 6-12 years in the inpatient setting and at home in a cross over design.
- Collection of glucose, insulin values to validate and improve the algorithms for insulin delivery for this age group.
- Collect faeces to describe the gut flora and its possible interaction with sensor functioning.

**Study design and Patient population**

**Design**

Randomised, 2 period cross over, open label trial to assess efficacy and safety of overnight closed-loop control to target insulin delivery versus open loop insulin delivery in children -with type 1 diabetes aged 6 to 12 years in the inpatient setting and at home. Patients will be randomized in equal numbers to one of the two sequences, (group A or B), which differ only with respect to the initial treatment with (A), or without (B) the overnight closed loop. (Figure 2)

Figure 2

**Patients**

Fifteen Children (to get evaluable data from 12) will be invited to participate with parental informed consent.

Inclusion criteria

- Between 6 - ≤12 years
- With type 1 diabetes for 6 months or more and
- Who use a pump for at least 6 months
- HbA1 should be <11 %.
- No medication or physical or psychological disease should be present, which could interfere with the study.

Written informed consent will be obtained (annex 1)

**Protocol**

Details about the visits and sampling procedure are summarised in table 1a and 1b.

After explanations and consent at visit 1 , the child will be randomised to start either with (group A) or without (group B) closed loop during the inpatient stay and 1 successive night at home.

All children will be invited twice for an overnight stay, once with and once without the closed loop system. During both overnight sessions blood samples will be taken for glucose and insulin measurements, to be used for further testing/improvement of algorithms requested for closing the loop by the Cambridge team.

At visit 2 around two weeks before these overnight stays, the family and patient are invited for a training session in the paediatric clinic. During this session, the DANA pump will be explained. Carb counting as well as technical knowledge on the use of this specific pump will be evaluated before going home.

When sufficient knowledge is acquired, the child will change towards the DANA pump ®. In the same session, we will start with a sensor freestyle Navigator

(Abbott ® ).

During the next two weeks prior to the overnight stay, diabetes control will be as usual , but with sensor and study pump .

Sufficient material will be either provided or prescribed (no extra cost for parents nor CNS)

Visit 3 (the day before the overnight stay in the clinic) will be at the clinic or at home. A new sensor (Navigator) will be placed. A second sensor (Dexcom G4 platinum) will be inserted to validate the Navigator glucose measurements, either at home or in the clinic. This sensor DEXCOM will need initial calibration 2 hrs later, requesting its placement before 1800. This visit will be used to evaluate the appropriate use of pump and sensor.

Visit 4 is the inpatient visit, where at Friday around 1600, the patient and parent(s) will come to the research ward.

The insulin catheter will be changed.

A local anaesthetic cream will be applied before the indwelling cannula is inserted for glucose and insulin measurements.

Blood samples will be taken according to the table 2b.

Stool samples will be collected, when produced, and directly frozen in -80°C (dry ice), or cryoshipper and will be transferred to the IBBL, for storage till measurement.

During the stay in the clinic a meal (content and carb will be decided before to be given at both hospital stays) will be provided in the ward and insulin bolus administration will be done by the parent according to their personal schedule, using the bolus wizard and before the meal. After the meal/bolus the **FlorenceD2 system** will be started in the group with **FlorenceD2 system on**, whereas in the other group their usual nocturnal insulin delivery will be given. A specialised nurse and /or physician will be present during these overnight stays to solve potential questions/problems.

Around 0700 breakfast is planned and in the **FlorenceD2 system on** group, the closed loop control is stopped, and the insulin bolus based on the personal bolus wizard is given followed by breakfast.

For the FlorenceD2 system **off** group, the insulin bolus is given based on the personal bolus wizard, followed by breakfast. Frequent sampling will be continued till 0930 (table 1b, pg16).

Around that time the iv cannula will be removed and the families will go home.

Sensors and pump treatment are maintained and in those randomised for overnight start, the family is invited to use the FlorenceD2 system again at home overnight after the evening bolus and till the next morning before the breakfast bolus. For any problems the dedicated diabetes hotline will be available 24/24 hrs. Training on FlorenceD2 will be provided on Visit 4.

At visit 5 (the Sunday, 24-36 hrs after the overnight stay) the pump catheter will be changed (every 3 days) , the CGM data will be downloaded, the DEXCOM sensor will be removed and one sensor ( Navigator) will not be changed . The FlorenceD2 system will be returned to the clinic and downloaded as well.

Insulin catheter will be changed again on Tuesday/Wednesday and Friday.

During the week the sensors will stay till the Thursday, day when the sensor will be changed. At visit 6, Thursday, (the day before the second overnight stay) , either at home or in the clinic the new sensors will be placed after EMLA.

Visit 7 , on Friday , will be once again in the clinic with an overnight stay with again either closed loop with sampling or control with sampling , and the same protocol will be applied as on visit 4 ( only an exchange of on- off).

The Saturday around 09.30 the family will go home again and use after dinner with the normal bolus the on or off FlorenceD2 system. On Sunday the study will be finished and a final visit (8) will take place in the clinic (or potentially at home). All devices will be returned and the pump catheter will be changed.

Downloads of sensors and pump will be performed in the clinic with the usual clinic technology. Depersonalised, encrypted downloads in ZIP format will be downloaded and used to analyse data. The questionnaires and CRF will stay in Luxembourg at the study center.

Blood samples will be taken according to the sample schedule. For insulin measurements the plasma will be stored till measurement at -20°C.

Venous whole blood Glucose will be measured using the I-Stat (, Glucose oxidase method ABBOTT ®) reporting a CV at 41 mg/dl of 1.6 % and 0.8 % in the higher range (289 mg/dl). Venous samples are around 7 mg/dl lower than capillary ones.

Venous plasma Insulin will be measured by an immunochemiluminometric assay ( invitron , Monmouth, UK) intra assay CV 4.7 % , inter assay CV 7,2-8,1%.

Faeces samples will be frozen, kept at IBBL till analysis. (24). Analysis will include high throughput sequencing.

During the whole study a dedicated and trained team will be available either in person or by phone.

Statistical analysis

A repeated measures regression model with an autoregressive first-order covariance structure adjusted for the period effect, and adjusted for glucose at 21:00, and based on the ranked normal transformation (if endpoints are not normally distributed) will be fit to compare the two treatments.

References

2 [Whittemore R](http://www.ncbi.nlm.nih.gov/pubmed?term=Whittemore R%5BAuthor%5D&cauthor=true&cauthor_uid=22581804), [Jaser S](http://www.ncbi.nlm.nih.gov/pubmed?term=Jaser S%5BAuthor%5D&cauthor=true&cauthor_uid=22581804), [Chao A](http://www.ncbi.nlm.nih.gov/pubmed?term=Chao A%5BAuthor%5D&cauthor=true&cauthor_uid=22581804), [Jang M](http://www.ncbi.nlm.nih.gov/pubmed?term=Jang M%5BAuthor%5D&cauthor=true&cauthor_uid=22581804), [Grey M](http://www.ncbi.nlm.nih.gov/pubmed?term=Grey M%5BAuthor%5D&cauthor=true&cauthor_uid=22581804).

Psychological experience of parents of children with type 1 diabetes: a systematic mixed-studies review. Diabetes Educ. 2012;38(4):562-79

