**This is the original document submitted to our national ethics committee before we started this specific study.**

**SPIDIMAN 01 protocol**

Synopsis

Title

Open label single centre randomized cross over study

to validate current algorithms and evaluate safety and efficacy of closed loop insulin delivery (FlorenceD2 system) in children with type 1 diabetes between 6 – 12 years of age

Objectives:

Long Term

Improve and facilitate diabetes management in children with

type 1 diabetes by closing the loop

Short term

- Validation of the algorithms for the overnight closed loop system in children with t1dm between 6-12 y in the clinic and at home. Collect glucose, insulin and insulin infusion rate data, helping to improve future ability of computer–based closed loop algorithms to control blood glucose in children with type 1 diabetes

Primary outcome

- Time spent in normal glucose range (70-144 mg/dl) of the children with type 1 diabetes 6-12 years with the use of an automated overnight closed loop pump uploaded with sensor and automated insulin feedback system without manual intervention overnight in the clinic and at home setting as measured by secondary CGM (start 1800, post dinner bolus, and till pre breakfast bolus 0730),

Secondary outcome (secondary CGM)

- Glucose variability (excursions) when treated with overnight closed loop in the clinic and at home (1800-0730)
- Time spent in hypoglycaemia (<60 mg/dl), as measured by the sensor, in the clinic and at home
- Time spent in hypoglycaemia (<70 mg/dl), as measured by the sensor, in the clinic and at home
- Time spent in hyperglycaemia (>180mg/dl,), as measured by the sensor, in the clinic and at home
- Comparison of the performance of two sensors at different site

Exploratory

- - User evaluation of the overnight closed loop.
  - Gut flora impact on glycaemic variability

Efficacy endpoint:

- Time spent with glucose values between 70-144 mg/dl (sensor measurements by secondary sensor) comparing the nights with and without automated insulin delivery (FlorenceD2 system with closed loop)
- Time spent in normoglycaemia (70-144 mg/ml as observed by blood glucose measurements) comparing the nights with and without automated insulin delivery

Safety endpoint

- Reduction in Time spent in hypoglycaemia as observed by blood glucose measurements during closed versus non closed loop
- Time spent in low glucose measurements (sensors, <60 mg/dl)

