**Visits time Action Questionnaires/Downloads**

V1 Detailed Information on protocol

Consent and randomisation CRF1

V2 -2 wks Training in the outpatient clinic to use the DANA CRF2

pump FFQ

Training to use the sensor Navigator Competency assessment

V3 d0* Change of sensor and adding second sensor, download CSII/CGM

providing EMLA to apply 1,5 hrs prior to the clinic visit V4

V4 d1 Arrival around 1600, Catheter change and

placement of indwelling venous cannula 24hRecall food intake

24h for sampling of insulin – glucose ( details in table 2b) CRF3

Start closed loop (group A) or open loop evaluation (group B)

after dinner (details in table 2b) Download CSII/CGM

When needed explanation to the family the handling of the

closed loop system (A)

d2 Closed loop (A) starting after dinner at home, stop next Download CSII/CGM°

morning before breakfast

V5 d3 Return FlorenceD2 closed loop system material Download CSII/CGM Change catheter CRF3.2

Problems encountered User Quality of Care1 Evaluation

d5 Change catheter at home (D5 or d6) Phone contact/Home/clinic visit

V6 d7* New sensors (dexcom/navigator) Download CSII/CGM

providing EMLA to apply 1,5 hrs prior to the clinic visit V7

V7 d8 Arrival around 1600 , change catheter ,

placement of indwelling venous cannula 24h Recall foodintake

for sampling of insulin – glucose ( details in table 2b) Download CSII/CGM

Start closed loop (B) or open loop (A) evaluation after dinner CRF3.3

(details in table 2b)

When needed explanation to the family the handling of the

closed loop system (B)

d9 Closed loop (B) starting after dinner at home, stop next Download CSII/CGM°  morning before breakfast

V8 d10 Change back to previous system Download CSII/CGM

Return AP CAM material CRF3.4

Discuss Problems encountered User Quality of Care evaluation

. .

Table 1b Sequence of the procedure

| Time | ACTION/meals and snacks | Plasma glucose | Plasma  insulin | CGM | CSII | BOLUS |
| --- | --- | --- | --- | --- | --- | --- |
| 1630 | Arrival at clinic  Canulation |  |  | X | X |  |
| 1700 | Start sampling | x | x | X | x |  |
| 1800 | Meal | x | x | X | x | X |
| 1830 | Start closed loop (A)  explain, training on starting and stopping closed loop start | x | x | X | x |  |
| 1900 | Play | X | x | X | x |  |
| 1930 | Play | x | x | X | x |  |
| 20.00 | Time for bed | x | x | X | x |  |
| 2100 | Lights out | x | x | X | x |  |
| 2200 |  | x | x | X | x |  |
| 2300 |  | x | x | X | x |  |

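### The only comparative model adjusts for glucose at 21:00, which is measured after closed loop has started and inside the outcome window, so it does not target the total effect on the stated outcome

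*Protocol*

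**What the plan says.** The Statistical analysis paragraph, at the end of the Protocol section, specifies a repeated-measures regression with first-order autoregressive covariance, "adjusted for the period effect, and adjusted for glucose at 21:00, and based on the ranked normal transformation" where endpoints are not normal. It is the only model given for comparing the treatments. The protocol does not label it as primary, gives no reason for choosing 21:00, does not say whether the value is blood or sensor glucose, and describes no analysis without the covariate.

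The Synopsis defines the primary outcome as "Time spent in normal glucose range (70-144 mg/dl) of the children with type 1 diabetes 6-12 years", measured by secondary CGM in the clinic and at home, over the window "start 1800, post dinner bolus, and till pre breakfast bolus 0730".

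Table 1b places the loop start in the clinic at "1830 | Start closed loop (A", that is, for group A at its first stay. Visit 7 repeats the procedure with the arms exchanged. For the home night the family is asked to "use the FlorenceD2 system again at home overnight after the evening bolus and till the next morning before the breakfast bolus", and no clock time is set. The 21:00 row of Table 1b reads "2100 | Lights out". Neither treatment nor the outcome window begins then.

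**The concern.** A baseline covariate should be a value that treatment cannot have influenced. Glucose is what closed loop acts on. By 21:00 on a closed-loop night the system has been running since dinner, while on the control night the child has had usual delivery. The 21:00 value is therefore partly a result of treatment, and it falls in the period over which time in range is counted.

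Conditioning on it asks a different question: how do nights compare given that they had the same glucose at 21:00? Whatever the loop achieved through the evening glucose level is credited to the covariate. The cross-over does not protect against this, because the covariate itself differs by treatment within the same child. At stake is the meaning of the only stated treatment comparison, in a trial expecting 12 completers and declaring significance at 5%.

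**Working it through.** The protocol states no effect size or power, so there is no figure of its own to reproduce. The check has three parts.

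**1. Clock times** (Synopsis and Table 1b)
- Outcome window: 18:00 to 07:30 = 13.5 h.
- Window start to covariate: 18:00 to 21:00 = 3.0 h; 3.0 / 13.5 = 22%.
- Loop start to covariate, clinic nights: 18:30 to 21:00 = 2.5 h.
- Home nights: the loop starts after the evening bolus. Exposure before 21:00 varies and cannot be computed.

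**2. What the adjustment does**

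For a linear model fitted to within-child differences:

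adjusted effect = total effect − b × D

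Here b is the slope of time in range on 21:00 glucose, and D is the closed-loop minus control difference in mean 21:00 glucose. The two effects agree only if b = 0 or D = 0.

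For scale, assume a total effect of 20 points. The Introduction quotes 40% to 60% in children and adolescents from a meta-analysis of earlier studies. The values of b and D are assumptions.

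| b (points per mg/dl) | D (mg/dl) | b × D (points removed) | Share of 20 |
|---|---|---|---|
| any | 0 | 0 | 0% |
| −0.1 | −10 | 1 | 5% |
| −0.2 | −20 | 4 | 20% |
| −0.3 | −30 | 9 | 45% |

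**3. Simulated nights** (all parameters assumed)

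*Loop acting from 18:30.* 20,000 pairs of nights were simulated in 5-minute steps from 18:00 to 07:30. Mean control glucose was 165 mg/dl, residual SD 45 mg/dl and autocorrelation time 4 h. The loop shrinks the distance from 118 mg/dl by up to 55%, approached with the time constant shown. The paired difference in time in range was regressed on the paired difference in the covariate.

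| Time constant (h) | Total effect | D at 21:00 (mg/dl) | Adjusted for 21:00 | Adjusted for 18:00 | Lost with 21:00 |
|---|---|---|---|---|---|
| 1 | 24.6 | −22.1 | 17.1 | 24.6 | 30% |
| 2 | 21.4 | −17.3 | 15.7 | 21.5 | 27% |
| 4 | 16.6 | −11.0 | 12.9 | 16.5 | 22% |
| 8 | 9.8 | −6.2 | 7.8 | 9.9 | 20% |

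Check of the first row with its fitted slope of −0.34: 24.6 − (−0.34 × −22.1) = 24.6 − 7.5 = 17.1. The 18:00 covariate recovers the total effect within simulation error.

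*Delayed action.* A second set assumed glucose SD 50 mg/dl, correlation time 1.5-3 h and a mean fall of 20-40 mg/dl.
- No delay: 15-33% lost.
- 1 h delay (onset constant 3 h): 12-21% lost.
- 2 h delay: 5-11% lost.
- Action beginning only at 21:00: about 0% lost.

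The loss is thus governed mainly by how much the loop has done by 21:00, and the protocol does not report that.

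**The case against.** The strongest objection concerns size. The Introduction says the algorithm sets basal rates, must handle delays in insulin absorption, and leaves meal boluses to be given manually. In the clinic the meal is the same at both stays and the parent gives the dinner bolus in both arms. Glucose in the first hours after dinner may therefore differ little between arms, and the bias could be small. This stands, and it is why the range must start at about zero. It does not rescue the covariate, because the plan would then be right only if the loop proved ineffective in its first 2.5 h.

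Other points that stand:
- The simulations use raw paired differences and many nights. The protocol's model is autoregressive, possibly rank-normal transformed, with about 12 children. The percentages do not transfer directly to its coefficient.
- Time in 70-144 mg/dl is not monotone in glucose. The bias is toward no effect only where high evening glucose predicts less time in range and the loop lowers it. Other patterns could reverse it.
- The 21:00 value predicts the night better. In the delayed-action runs it cut the SD of the paired difference by about 5-13%, against 3-6% for an 18:30 value. This partly offsets the loss in the test statistic but does not restore the intended effect.
- The protocol calls itself a feasibility study and waives power. It still defines efficacy endpoints comparing nights and sets a 5% level.

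Two defences fail. Treating 21:00 as the start of the night conflicts with a window opening at 18:00, and moving the window to 21:00 would still leave the covariate post-treatment. Nor is this a detail left to an analysis plan, since the protocol itself names the covariate and the clock time.

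A reader might infer that the model is bound to understate closed loop by some known fraction, or that it produces false positives. The document supports neither. The fraction rests on assumptions, and by the identity above, if the loop changes nothing, both the total and the adjusted effects are zero.

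**Conclusion.** The covariate is wrong as written. On clinic nights it is measured 2.5 h into treatment and 22% of the way through the outcome window. On home nights it follows a loop start with no fixed time. The treatment coefficient does not in general estimate the total effect of overnight closed loop on 18:00-07:30 time in range once the loop has changed glucose by 21:00. Because this is the only comparative model stated, it is reasonable to take it as governing the primary outcome, although the protocol does not say so.

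The timing error is certain; its consequence in points is not. Under the assumed dynamics the loss runs from about 0% to about one third of the effect. One third is not a bound: the most extreme combination in the linear check gives 45%. The expected direction is toward no effect if the loop lowers high evening glucose.

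**What to change.** In the Statistical analysis paragraph, replace glucose at 21:00 by a pre-loop glucose taken at the same point and from the same source on every night, closed-loop and control, clinic and home. The secondary-CGM value at the dinner bolus serves, which is 18:00 in the clinic.

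The 18:30 value should not be used: that row of Table 1b is itself the loop start, and it lies inside the outcome window. Venous samples should not be combined with sensor values, because venous sampling is scheduled only for the clinic nights and the covariate would then mix two methods. If the 21:00-adjusted model is of interest, keep it as a sensitivity analysis labelled as conditioning on a post-treatment value. Any separate analysis plan should carry the same wording.

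The cost is one line of text and no new data: the second sensor is placed the day before each clinic stay and worn through the following home night. The downside is that an earlier covariate may explain somewhat less variance than the 21:00 value.

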**Data analysis**

Questionnaire data will be entered on paper and data entry in the data base will be performed in Luxembourg , study center Clinique Pédiatrique de Luxembourg.

The sensor data and pump data will be read through the routine source , used for clinical practice in the CHL. Depersonalised, encrypted downloads in ZIP format will be downloaded and used to analyse data in Cambridge ,UK

Blood glucose and insulin values , will be entered into the data base dedicated for the study and depersonalised transferred to the UK Cambridge group .

In general a 5% significance will be used to declare statistical significance .

Both glucose data obtained through the sensors will be compared with the blood glucose values.

The time in target and the different mentioned indicators will be calculated comparing the data obtained with and without the closed loop in the inpatient and home setting .

A comparison will be made between the data obtained at home and in the clinic .

All blood glucose and sensor data will be analysed anonymously , eg the person analysing the data will be blinded for the type of overnight profile

Finally glucose and insulin values will serve for improved algorithm development by the CAM team, ( prof [name] and [name]) university of Cambridge, UK

CRF1 Name STUDY number

Written Consent yes ☐ Study number

Gender F ☐ M ☐ Randomisation A☐ B ☐

DoB …./…./….

Date Diagnosis :

Date Start pump treatment PUMP type

Number of Severe hypoglycemic events over the last 3 months ☐☐

Number of severe DKA events over the last 12 months ☐☐

Frequency of BG measurement

Medication during the last 48 hours , other than insulin yes : ☐ no☐

If yes : please specify :

Concomittant disease : coeliac ☐ thyroid ☐ other ☐

Family situation :…………………………..

Ethnicity : Caucasian ☐, Black ☐ , Asian ☐ Hispanic ☐ other

CLINICAL DATA

BW kg Height cm

BP mmHg Normal clinical examination yes ☐ no ☐

If not, please specify

Intercurrent infections : yes ☐ no ☐ ,

If yes , please specify

Pump type

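### The comparative model has no clinic/home term although the primary outcome covers both settings; if the four nights are pooled, the standard error is too wide, but the estimate is not biased

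*Protocol*

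**What the plan says.** The Synopsis states one primary outcome, time in 70-144 mg/dl, measured "without manual intervention overnight in the clinic and at home setting as measured by secondary CGM". Under Design, "Patients will be randomized in equal numbers to one of the two sequences", which differ in whether closed loop comes first or second. In each period the allocated treatment applies "during the inpatient stay and 1 successive night at home". Table 1a shows the four nights: clinic d1, home d2, clinic d8, home d9.

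The Statistical analysis paragraph gives one model for comparing the treatments, a repeated measures regression with first-order autoregressive covariance, "adjusted for the period effect, and adjusted for glucose at 21:00, and based on the ranked normal transformation" if endpoints are not normal. Setting is not among the adjustments.

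Data analysis adds that time in target and the other indicators will be calculated "comparing the data obtained with and without the closed loop in the inpatient and home setting". It also says that home and clinic data will be compared, without naming a model or term for this. Nowhere does the protocol say whether the stated model is fitted to all four nights together or to each setting separately.

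**The concern.** The two kinds of night differ by design. Clinic nights have a pre-agreed ward meal, staff on hand, a venous cannula and mostly hourly sampling. The insulin catheter is changed on arrival for the clinic night and next on d3 or d10, so each home night runs on an older catheter. The secondary sensor, which measures the primary outcome, goes in the day before the clinic night and is a day older at home. A systematic difference in time in range between settings is therefore plausible, and setting is known for every night.

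In a pooled fit without a setting term, that difference is treated as random night-to-night variation. Because the nights alternate clinic, home, clinic, home, it also lowers the estimated correlation between neighbouring nights. At stake is precision with 12 completers. In addition, the stated model cannot deliver the home-versus-clinic comparison that the protocol promises.

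**Working it through.** **Inputs from the protocol.** 12 completers (15 enrolled), two equal sequences, four nights per child, 5% significance. A power calculation is declared not applicable, so there is no figure to reproduce.

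**Assumptions not in the protocol.** Night-level SD 20 percentage points; correlation 0.4 between successive nights; home-minus-clinic difference δ of 0, 10 or 20 points; two-sided test; the four nights treated as equally spaced occasions. The 21:00 glucose covariate and the rank transformation are left out.

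**1. Bias with complete data.** 12 children × 4 nights = 48 nights, 12 in each treatment-by-setting cell. Each treatment has 12 home nights out of 24, so the setting difference entering the treatment contrast is δ × (12/24 − 12/24) = 0.

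**2. Where the difference goes.** Without the term, each night lies δ/2 above or below the mean according to setting. This adds δ²/4 to the residual variance and subtracts δ²/4 from the covariance of neighbouring nights (0.4 × 400 = 160).

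| δ | Variance 400 + δ²/4 | SD | Neighbour correlation |
|---|---|---|---|
| 0 | 400 | 20.0 | 160/400 = 0.40 |
| 10 | 425 | 20.6 | 135/425 = 0.32 |
| 20 | 500 | 22.4 | 60/500 = 0.12 |

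REML AR(1) fits to simulated trials (400 runs per scenario) gave SD 20.6 with correlation 0.30, and SD 22.4 with correlation 0.11, in agreement.

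**3. Standard error by hand.** Take the mean of a child's two closed-loop nights minus the mean of the other two. Under AR(1) the variance over 12 children is σ²(4 + 2ρ − 4ρ² − 2ρ³)/48.
- δ = 0: 400 × 4.032/48 = 33.6, SE 5.80
- δ = 10: 425 × 4.167/48 = 36.9, SE 6.07 (ratio 1.05)
- δ = 20: 500 × 4.179/48 = 43.5, SE 6.60 (ratio 1.14)

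**4. Standard error from the fitted model.**

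| δ | Mean SE without term | With term | Ratio | True sampling SD without / with |
|---|---|---|---|---|
| 10 | 5.82 | 5.49 | 1.06 | 5.62 / 5.60 |
| 20 | 6.37 | 5.49 | 1.16 | 5.61 / 5.59 |

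The estimate is no more variable without the term; only its reported SE grows. With an exchangeable true correlation the ratios are 5.77/5.47 = 1.05 and 6.30/5.40 = 1.17. A second simulation with other variances (child SD 12, child-by-period 8, night 15) gave 5.9/5.6 = 1.05 and 6.5/5.6 = 1.16.

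**5. The test.** Null rejection was 3.5% without and 4.8% with the term at δ = 10, and 3.3% versus 4.3% at δ = 20 (Monte Carlo error about √(0.05 × 0.95/400) = 1.1 points). For a 20-point effect, the size of the 40% to 60% change cited in the Introduction, power was 92% versus 94% and 90% versus 95%. In the second simulation, for a 12-point effect, it was 41% versus 46% and 35% versus 47% (Monte Carlo error about 3 points).

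**6. Dependence on spacing.** If the AR(1) used calendar days (gaps of 1, 6 and 1), correlations across weeks would be negligible (0.4⁶ = 0.004) and the variance becomes σ²(4 + 4ρ)/48. This gives (1600 + 640)/48, (1700 + 540)/48 and (2000 + 240)/48, all 46.7. The loss in step 4 then disappears.

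**7. Bias if m closed-loop home readings were lost.** Leak under simple averaging = δ × [(12 − m)/(24 − m) − 1/2].
- m = 3: 9/21 − 1/2 = −0.071, so −0.7 (δ = 10) or −1.4 (δ = 20) points
- m = 6: 6/18 − 1/2 = −0.167, so −1.7 or −3.3 points

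The AR(1) fit gave −1.0 and −1.6 for m = 3, and −2.1 and −3.7 for m = 6. The sign follows that of δ.

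**The case against.** **Separate analyses per setting.** The Data analysis sentence can be read as one comparison in the clinic and one at home. No setting term is then needed and the SE problem does not arise. This reading is possible. But it turns the single primary outcome into two tests with neither named as primary. It also leaves the autoregressive structure with little to do: with two nights per child it is just one correlation. That suggests a four-night fit without proving it.

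**Left to the SAP.** A SAP may settle pooling and the full list of fixed effects. However, the protocol is not silent here. It names the covariance structure and lists the adjustments, and a known design factor is not among them.

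**Small and assumption-driven.** This stands in part. Every SD and clinic-home difference is assumed, the 21:00 covariate could absorb some of the difference, and power carries limited weight in a declared feasibility study.

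**A stronger reading to avoid.** Because "the family is invited to use the FlorenceD2 system again at home overnight", a reader might infer that closed-loop home nights will often be missing and that the treatment effect will be biased. The document does not support this. It uses the same verb for the inpatient stays and the training session. The home night is part of the randomised allocation and is scheduled in Table 1a. The secondary sensor is not linked to the controller and stays in place until the Sunday visit, so a night without the loop still yields an outcome under the allocated treatment.

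**Conclusion.** The point holds in a limited form. The only stated comparative model omits setting, while the primary outcome covers both settings and a home-versus-clinic comparison is promised. If the four nights are pooled with an ordinary equally spaced AR(1), the model SE is about 6% too wide at an assumed 10-point clinic-home difference and 16% at 20 points, and the test is conservative. With complete data there is no bias. Under calendar-day spacing or separate analyses the SE loss vanishes, but the questions of what the primary comparison is and how the settings are to be compared remain. Bias of roughly 1 to 4 points would need 3 to 6 of 12 closed-loop home readings to be lost with none lost in the control condition, and nothing in the protocol points to that. This is a worthwhile improvement to the model, not an error that invalidates it.

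**What to change.** State in the Statistical analysis paragraph that the primary analysis pools clinic and home nights and is *adjusted for the period effect and for setting (clinic or home night), with a treatment-by-setting term; the closed-loop effect is reported overall, averaged equally over the two settings, and for each setting with a 95% interval*. Treat the setting main effect as a nuisance term. The treatment-by-setting term supplies the home-versus-clinic comparison of the closed-loop effect. If separate analyses are intended instead, say so and name which one is primary.

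The cost is one sentence and one or two error degrees of freedom out of 48 nights. No new data are needed, because setting is known for every night.
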